### Permitted and prohibited co-interventions

Participants in both groups may continue pharmacological treatments prescribed by their primary care providers, including analgesics, antidepressants, or anticonvulsants commonly used in FM management. They will be instructed not to initiate any new structured physical therapy, exercise program, or cognitive behavioural therapy during the trial. Engagement in such interventions outside the study protocol will be considered a protocol deviation.

At each assessment point, participants will report any additional treatments, medications, or health-related changes. These data will be documented and included as potential covariates in subsequent analyses.

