### Participant selection, recruitment, and consent

Participants will be identified through professional networks of the research team and outreach initiatives by collaborating centers in Latin America. Trained study personnel will verify eligibility using medical records and structured interviews.

Eligible individuals will be contacted via telephone or videoconference and provided with a digital information sheet describing study objectives, procedures, potential risks, and benefits. Informed consent approved by institutional ethics committees will be obtained electronically prior to baseline assessment or intervention initiation.

Following consent, participants will complete baseline demographic, clinical, and functional evaluations before randomization (Figs 1 and 2).

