### Secondary outcomes

Secondary endpoints will provide complementary information on physical, psychosocial, and quality-of-life domains:

Impact of fibromyalgia (FIQ-R; 0–100, higher scores = greater impact) The Spanish version has demonstrated high internal consistency (Cronbach’s α ≥ 0.91) and acceptable test-retest reliability (ICC ≥ 0.70 for total score) [30,31]Lower limb strength and endurance (30-Second Sit-to-Stand Test, validated for remote FM assessment) [32]Health-related quality of life (EQ-5D-3L, index −0.59 to 1, higher = better) [33]Psychological well-being (NRS-Anxiety; 0–10, higher = greater anxiety) [34]Exploratory outcome: Perceived barriers to adherence, assessed with the Treatment Adherence Barriers Questionnaire (adapted for telerehabilitation) [35]

All outcomes will be assessed at baseline (week 0) and post-intervention in week 13 (±7 days). No long-term follow-up is planned. Instruments were selected based on prior validation for remote administration, relevance to FM, and consistency with outcome domains recommended for digital rehabilitation trials [28,36].

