### Data analysis

Analyses will follow both intention-to-treat (ITT) and per-protocol (PP) principles, consistent with CONSORT recommendations [21]. The ITT population will include all randomised participants, analysed according to their allocated group. Missing outcome data will be addressed using multiple imputation, assuming data are missing at random. Sensitivity analyses using last observation carried forward (LOCF) and complete-case approaches will be performed to assess the robustness of the findings.

The PP population will include participants who complete at least 80% of the prescribed intervention dose (≥29/36 exercise sessions and ≥10/12 PNE modules) and have no major protocol deviations. Baseline characteristics will be summarised descriptively and compared between groups using parametric (independent t-test) or non-parametric (Mann–Whitney U test) methods, depending on normality assessed via the Shapiro–Wilk test.

The primary analysis will evaluate the change in pain intensity (VAS, 0–10 cm) from baseline to week 13 (±7 days) between groups using both independent t-tests and Mann–Whitney U tests to ensure consistency of results. The anticipated effect size (Cohen’s d ≈ 0.65) was derived from prior trials of multidisciplinary and digital interventions in fibromyalgia, which reported moderate-to-large effects on pain reduction (range 0.5–0.7) [28,36,37]. Within-group changes will be assessed using paired t-tests or Wilcoxon signed-rank tests, as appropriate. Effect sizes (Cohen’s d) with 95% confidence intervals will be reported and interpreted using conventional thresholds [38].

Secondary outcomes (FIQ-R, 30-Second Sit-to-Stand, EQ-5D, NRS-Anxiety, adherence barriers) will be analysed using similar methods. Minimal clinically important differences (MCIDs) will be defined a priori as follows: 14% for FIQ-R total score, ≥ 2 repetitions for the 30-Second Sit-to-Stand, and ≥0.07 for EQ-5D index, based on previous validation studies. For repeated measures, mixed-effects models will account for within-subject correlations and time effects [39,40]. Multivariable regression analyses will adjust for relevant covariates (e.g., baseline pain, age, pharmacological treatment).

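### Co-treatments and health changes reported at week 13, after randomisation, are allowed as covariates in the adjusted analyses

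*Protocol article*

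**What the plan says.** Under Permitted and prohibited co-interventions, the protocol article states: "At each assessment point, participants will report any additional treatments, medications, or health-related changes". The next sentence gives the use: "These data will be documented and included as potential covariates in subsequent analyses". Neither sentence is limited to baseline values.

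Trial design and context, Primary outcome and Secondary outcomes give two assessment points only, week 0 and week 13 (±7 days). Participant selection, recruitment, and consent fixes the order at entry: "participants will complete baseline demographic, clinical, and functional evaluations before randomization".

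Drug treatment is not frozen during the trial: "Participants in both groups may continue pharmacological treatments prescribed by their primary care providers". What participants are told not to start is structured physical therapy, an exercise programme or cognitive behavioural therapy.

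Data analysis makes the primary comparison of VAS change "using both independent t-tests and Mann–Whitney U tests to ensure consistency of results", with no covariates. Later in that section it adds: "Multivariable regression analyses will adjust for relevant covariates". The examples given there are baseline pain, age and pharmacological treatment. The list is open, and only pain carries the word baseline.

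**The concern.** A covariate recorded before randomisation cannot be affected by allocation, so adjusting for it leaves the treatment comparison valid. A covariate recorded at week 13 has no such protection. Participants whose pain does not improve may add analgesics, and those who improve may drop them. A reported health change can be nearer still to the outcome, because worse pain may itself be reported as one.

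Holding such a variable fixed compares participants who have been made alike on something that treatment and pain response helped to produce. The resulting coefficient is not the effect of being assigned to the programme, even with perfect randomisation and complete data. It also sits badly with the intention-to-treat aim stated in Data analysis.

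A second, smaller matter is choice. If the covariates are only potential, they can be settled after the co-treatment data are seen. With 50 participants, that choice could visibly move an adjusted estimate.

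**Working it through.** **Timing.** There are two assessment points, and baseline evaluation precedes randomisation. Week-0 reports are therefore legitimate covariates and week-13 reports are post-randomisation. Reports of additional treatments and of changes will mostly arise at week 13. The covariate sentence covers both points without distinction.

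**Where the data could enter.** The primary t-test and Mann–Whitney U test take no covariates, so the data cannot enter there. They can enter the multivariable regressions and any other adjusted analysis.

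**Size, as an illustration.** The plan states no figure to reproduce. Inputs:

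- Effect −2.0 cm and SD 3.0 cm, from Sample size, with the SD taken here as the within-arm SD of change (assumption).
- M = 1 if the participant reports added medication at week 13, with P(M = 1) = 1 / (1 + exp(−s(change − c))). The slope s (log-odds per cm) and centre c are assumptions; the documents give no rate of medication change.
- The added medication has no effect on pain (relaxed below).

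For least squares of change on arm and M, with equal arms:

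- b = (cov₀ + cov₁) / (v₀ + v₁), where cov is the within-arm covariance of change with M, v = P(1 − P), and subscripts 0 and 1 are control and intervention
- adjusted effect = −2.0 − b × (P₁ − P₀)

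Evaluated by numerical integration:

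| s | c | P₀ | P₁ | b | Adjusted effect | Shrinkage |
|---|---|---|---|---|---|---|
| 0.1 | 2.0 | 0.451 | 0.403 | 0.88 | −1.96 cm | 2% |
| 0.2 | 2.0 | 0.409 | 0.323 | 1.67 | −1.86 cm | 7% |
| 0.4 | 2.0 | 0.349 | 0.220 | 2.88 | −1.63 cm | 18% |
| 0.6 | 0.5 | 0.452 | 0.273 | 3.54 | −1.37 cm | 32% |

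Last row in full: b = (0.862 + 0.718) / (0.248 + 0.199) ≈ 3.54, and −2.0 − 3.54 × (0.273 − 0.452) ≈ −2.0 + 0.63 = −1.37. A simulation of one million participants gives −1.62 and −1.36 for the last two rows, the same within simulation error. The unadjusted estimate stays at −2.0 cm throughout.

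**Relaxing the inert medication.** Suppose the added medication lowers pain by d cm and its use depends on the change that would have occurred without it. The arm coefficient in the adjusted model is unchanged, because d is absorbed by the coefficient of M. The effect of assignment becomes −2.0 + d × 0.179 in the last row: −1.91 cm for d = 0.5 and −1.82 cm for d = 1.0. The adjusted −1.37 cm is still 28% and 25% smaller in size. The distortion does not depend on the medication being inert.

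**The case against.** Most of the case on the other side concerns reach, and much of it stands.

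- A reader might infer that the trial's main result is biased. The documents do not support this, because the primary comparison has no covariates.
- A reader might infer that the plan requires adjustment for week-13 data. It does not. The data are potential covariates, no model is named, and each assessment point includes baseline, where adjustment is sound.
- A reader might take pharmacological treatment in Data analysis to mean week-13 use. The entry value is the more natural reading. Table 1 lists it under clinical data beside diagnosis duration and comorbidities, clinical evaluation comes before randomisation, and the subgroup list sets it beside baseline pain and age. Adding the word baseline is a clarification.
- The statistician and principal investigator are blinded until database lock, which limits but does not remove allocation-informed choice of covariates.
- The larger shrinkage figures need strong dependence of medication on pain change. Weak dependence gives only a few per cent.
- A final covariate list may properly sit in an analysis plan that is not shown.

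The last point does not dispose of the matter. The criticism is of a use that the protocol states, and not of detail that it omits. The planned regressions are part of the analysis, and nothing in the document keeps week-13 reports out of them.

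**Conclusion.** The point holds, within limits. The co-interventions section permits covariates that allocation and pain response can influence, and an adjusted estimate using them would not estimate the effect of assignment. The unadjusted primary tests are untouched.

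That conclusion rests on timing alone and needs no figure. The illustrated shrinkage, about 2% to 32%, rests wholly on the assumed slopes, reporting rates and causal structure. It should not be read as a forecast, nor as showing that the bias must run toward a smaller effect. This should be corrected, as a wording change that bears on the non-primary adjusted analyses.

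**What to change.** Replace the covariate sentence under Permitted and prohibited co-interventions with wording to this effect: covariates in adjusted treatment-effect analyses are limited to values recorded before randomisation (for example baseline VAS, age stratum and baseline pharmacological treatment); co-interventions, medication changes and health changes during follow-up are summarised by arm and are not adjusted for in those analyses; any analysis that uses them is labelled exploratory. A complete ban on analysing follow-up co-treatment is not needed.

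For clarity, write baseline pharmacological treatment in the regression sentence of Data analysis and in the subgroup definition.

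The cost is a few phrases, with no new data or staff time. The article states that no participants had been recruited at submission, and Protocol amendments gives the route for a change in analytical strategy. The one downside is that the adjusted model cannot account for imbalance in follow-up co-treatment, which is then only described.

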### Outcomes

Outcome selection followed the IMMPACT recommendations for chronic pain clinical trials [28] and was tailored to the characteristics of FM and the digital delivery format (Table 1).

**Table 1 pone.0349017.t001:** Description of the measurements.

Variable Category	Variable	Dimension	Indicator	Value
**Sociodemographic Data**	Age	Chronological age	Number of complete years	18 to 65 years
	Gender	Gender identification	Participant-reported gender	Male / Female
	Educational level	Formal schooling level	Highest level completed	Primary / Secondary / Technical / University / Postgraduate
	Residence location	Geographical context	Living area	Urban / Rural
	Access to technology	Digital inclusion	Availability of internet-connected devices	Yes / No
	Employment status	Work situation	Current working status	Employed / Unemployed / Informal / Retired
**Clinical Data**	Diagnosis duration	Time since FM diagnosis	Time elapsed since official diagnosis	Numerical (months)
	Pharmacological treatment	Medication type and dose	Use of prescribed drugs	Analgesics, antidepressants, anticonvulsants (type, dose, frequency)
	Comorbidities	Associated diseases	Presence of additional chronic conditions	Yes / No (specify if relevant)
**Primary Outcomes**	Pain intensity	Subjective pain perception	Visual Analogue Scale (VAS)	0 (no pain) to 10 (worst imaginable pain)
**Secondary Outcomes**	Impact of FM	Functional limitation and symptom severity	Total score of the FIQ-R	0 to 100 (higher scores indicate worse impact)
	Lower limb function	Strength and endurance	30-Second Sit-to-Stand Test	Number of repetitions in 30 seconds
	Quality of life	Health-related QoL	EQ-5D index	−0.59 to 1.0 (higher = better QoL)
	Anxiety	Psychological distress	Numeric Rating Scale for Anxiety (NRS-A)	0 (no anxiety) to 10 (worst possible anxiety)
	Adherence barriers	Perceived obstacles to treatment	Treatment Adherence Barriers Questionnaire	Categorized: logistical, motivational, contextual, etc.

Table note: Abbreviations: FM = Fibromyalgia; VAS = Visual Analogue Scale; FIQ-R = Revised Fibromyalgia Impact Questionnaire; EQ-5D = EuroQol-5 Dimensions; NRS-A = Numeric Rating Scale for Anxiety.

### Primary outcome

The primary endpoint is change in pain intensity (VAS) between baseline (week 0) and post‑intervention at week 13 (±7 days), immediately after completion of the 12‑week programme. Secondary endpoints will be assessed at the same timepoints [29]. Pain intensity was chosen as the primary outcome because it is the cardinal symptom of FM and the most consistently recommended endpoint in chronic pain trials [28].

### Secondary outcomes

Secondary endpoints will provide complementary information on physical, psychosocial, and quality-of-life domains:

Impact of fibromyalgia (FIQ-R; 0–100, higher scores = greater impact) The Spanish version has demonstrated high internal consistency (Cronbach’s α ≥ 0.91) and acceptable test-retest reliability (ICC ≥ 0.70 for total score) [30,31]Lower limb strength and endurance (30-Second Sit-to-Stand Test, validated for remote FM assessment) [32]Health-related quality of life (EQ-5D-3L, index −0.59 to 1, higher = better) [33]Psychological well-being (NRS-Anxiety; 0–10, higher = greater anxiety) [34]Exploratory outcome: Perceived barriers to adherence, assessed with the Treatment Adherence Barriers Questionnaire (adapted for telerehabilitation) [35]

All outcomes will be assessed at baseline (week 0) and post-intervention in week 13 (±7 days). No long-term follow-up is planned. Instruments were selected based on prior validation for remote administration, relevance to FM, and consistency with outcome domains recommended for digital rehabilitation trials [28,36].

### Multiplicity

As pain intensity (VAS) is the sole primary endpoint, secondary outcomes will be considered exploratory. No formal multiplicity adjustment will be applied; effect estimates will be reported with 95% confidence intervals to aid interpretation.

### Data analysis

Analyses will follow both intention-to-treat (ITT) and per-protocol (PP) principles, consistent with CONSORT recommendations [21]. The ITT population will include all randomised participants, analysed according to their allocated group. Missing outcome data will be addressed using multiple imputation, assuming data are missing at random. Sensitivity analyses using last observation carried forward (LOCF) and complete-case approaches will be performed to assess the robustness of the findings.

The PP population will include participants who complete at least 80% of the prescribed intervention dose (≥29/36 exercise sessions and ≥10/12 PNE modules) and have no major protocol deviations. Baseline characteristics will be summarised descriptively and compared between groups using parametric (independent t-test) or non-parametric (Mann–Whitney U test) methods, depending on normality assessed via the Shapiro–Wilk test.

The primary analysis will evaluate the change in pain intensity (VAS, 0–10 cm) from baseline to week 13 (±7 days) between groups using both independent t-tests and Mann–Whitney U tests to ensure consistency of results. The anticipated effect size (Cohen’s d ≈ 0.65) was derived from prior trials of multidisciplinary and digital interventions in fibromyalgia, which reported moderate-to-large effects on pain reduction (range 0.5–0.7) [28,36,37]. Within-group changes will be assessed using paired t-tests or Wilcoxon signed-rank tests, as appropriate. Effect sizes (Cohen’s d) with 95% confidence intervals will be reported and interpreted using conventional thresholds [38].

Secondary outcomes (FIQ-R, 30-Second Sit-to-Stand, EQ-5D, NRS-Anxiety, adherence barriers) will be analysed using similar methods. Minimal clinically important differences (MCIDs) will be defined a priori as follows: 14% for FIQ-R total score, ≥ 2 repetitions for the 30-Second Sit-to-Stand, and ≥0.07 for EQ-5D index, based on previous validation studies. For repeated measures, mixed-effects models will account for within-subject correlations and time effects [39,40]. Multivariable regression analyses will adjust for relevant covariates (e.g., baseline pain, age, pharmacological treatment).

Pre-specified subgroup analyses will explore treatment effects according to baseline pain severity (VAS ≥ 7 vs. < 7), age group (<50 vs. ≥ 50 years), and pharmacological treatment status (yes/no). Secondary outcomes will be considered exploratory. No formal multiplicity adjustment will be applied; effect estimates will be reported with 95% confidence intervals to support interpretation

All statistical tests will be two-tailed with α = 0.05. Analyses will be performed using IBM SPSS Statistics v28.0 and R software v4.3.2. Results will be presented with effect sizes, confidence intervals, and graphical summaries.

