### Sample size

The sample size was calculated a priori to ensure both feasibility and statistical rigor. The calculation targeted the primary endpoint of pain intensity (VAS, 0–10 scale) from baseline to week 13. A minimal clinically important difference (MCID) of 2.0 cm and an expected standard deviation (SD) of 3.0 cm were assumed, based on previous randomized controlled trials in fibromyalgia populations evaluating pain reduction through behavioral and digital interventions [28,35]. Under these parameters, a total sample of 50 participants (25 per group) provides 80% power (two-tailed, α = 0.05) to detect a moderate-to-large effect size (Cohen’s d ≈ 0.65), using an independent t-test. The calculation was performed using G*Power software (version 3.1.9.6).

An attrition rate of approximately 10% was anticipated. Although higher dropout rates have been reported in some digital health trials, this estimate was considered reasonable given the structured follow-up, the short intervention period (13 weeks), and previous experience from our group showing high retention (>90%) in similar telehealth interventions for chronic pain. The sample size remains adequate after accounting for this expected loss. This calculation was finalised prior to recruitment to ensure prospective justification.

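### With only baseline and week 13 measured, LOCF is baseline carried forward and complete-case stays close to the MAR imputation, so the planned sensitivity analyses do not explore informative dropout over a plausible range

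*Protocol article*

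**What the plan says.** Under Data analysis, the protocol article sets the main approach: "Missing outcome data will be addressed using multiple imputation, assuming data are missing at random". The robustness check follows directly: "Sensitivity analyses using last observation carried forward (LOCF) and complete-case approaches will be performed to assess the robustness of the findings". No delta-adjusted, tipping-point, reference-based or other missing-not-at-random analysis is named.

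The visit schedule is fixed elsewhere. Under Secondary outcomes: "All outcomes will be assessed at baseline (week 0) and post-intervention in week 13", and "No long-term follow-up is planned". Trial design and Primary outcome give the same two timepoints. The monthly staff contacts described under Intervention fidelity and adherence monitoring serve to verify participation; no interim VAS is mentioned.

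The primary comparison of VAS change is made "between groups using both independent t-tests and Mann–Whitney U tests to ensure consistency of results". Under Sample size: "An attrition rate of approximately 10% was anticipated". That section also acknowledges that some digital health trials lose more, without giving a figure.

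**The concern.** LOCF was devised for trials with several post-baseline visits. With only one, the last observation of anyone missing week 13 is the baseline value, and the imputed change is zero by construction. Complete-case, for its part, rests on nearly the same condition as imputing week 13 from baseline.

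The worry is dropout related to the unseen outcome, and the document makes that plausible. Its Discussion names high attrition, kinesiophobia and fear-avoidance as obstacles to exercise programmes, and its Discontinuation criteria include clinical deterioration and persistent non-adherence. If the imputation, complete-case and LOCF results agree, the report will call the finding robust, although only one arbitrary departure from MAR has been looked at. With about 45 of 50 participants observed, that is a thin basis for the claim.

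**Working it through.** The missing-data text contains no figure to reproduce. The stated 80% power is a separate matter, and nothing below depends on it.

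**Inputs from the protocol:** difference 2.0 cm, SD 3.0 cm, 25 per arm, 10% attrition. **Assumptions:** mean improvements of 3 cm (intervention) and 1 cm (control); every dropout rate other than 10%; the split of dropout between arms; the missingness models in step 3. Differences are benefits in favour of the intervention.

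**1. Expected LOCF difference.** Let m be the share missing (T intervention, C control) and μ the mean improvement, with missing participants like observed ones. Since LOCF gives them zero change, the difference is (1 − mT)·μT − (1 − mC)·μC.

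| Missing T / C | μT, μC (cm) | Truth | LOCF |
|---|---|---|---|
| 10% / 10% | 3, 1 | 2.0 | 2.70 − 0.90 = 1.80 |
| 20% / 20% | 3, 1 | 2.0 | 2.40 − 0.80 = 1.60 |
| 30% / 10% | 3, 1 | 2.0 | 2.10 − 0.90 = 1.20 |
| 5% / 15% | 3, 1 | 2.0 | 2.85 − 0.85 = 2.00 |
| 5% / 30% | 3, 1 | 2.0 | 2.85 − 0.70 = 2.15 |
| 5% / 25% | 2, 2 | 0 | 1.90 − 1.50 = 0.40 |

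The bias can go either way.

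**2. Standard error at 10% missing.** Complete-case with 22.5 per arm on average: 3·√(2/22.5) = 0.89 cm. For LOCF the variance per arm is (1 − m)·σ² + m(1 − m)·μ²:
- intervention: 8.10 + 0.81 = 8.91
- control: 8.10 + 0.09 = 8.19
- SE = √((8.91 + 8.19)/25) = 0.83 cm

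This is below even the 3·√(2/25) = 0.85 cm of a trial with no missing data, because the zeros are treated as observed.

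**3. Complete-case against MAR imputation.** Simulation with 500,000 per arm, imputing by regression on baseline within arm:

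| Missingness depends on | Missing T / C | Truth | Complete-case | MAR imputation | LOCF |
|---|---|---|---|---|---|
| baseline | about 10% / 10% | 2.003 | 2.005 | 2.005 | 1.800 |
| unseen change, intervention arm | about 5% / 5% | 1.995 | 2.140 | 2.137 | 2.018 |
| unseen change, control arm | 4% / 20% | 2.000 | 2.382 | 2.373 | 2.390 |

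Complete-case and MAR imputation nearly coincide throughout. In the last row, where controls who improved most are likeliest to be missing, all three analyses agree and all are about 0.4 cm too large.

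**4. What a delta analysis shows.** Add δ to imputed week 13 VAS (positive is worse). The benefit becomes the MAR benefit − mT·δT + mC·δC. From 2.0 cm:
- 10% missing in the intervention arm, δT = 1 or 3, δC = 0: 1.9 or 1.7 cm.
- 20% missing in the intervention arm, same shifts: 1.8 or 1.4 cm.
- Opposite shifts δT = +3, δC = −3: 2.0 − 0.3 − 0.3 = 1.4 cm at 10% in both arms, and 2.0 − 0.6 − 0.6 = 0.8 cm at 20%.

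In these terms, LOCF is the single point δT = 3, δC = 1 (2.0 − 0.3 + 0.1 = 1.8 cm at 10%). Its deltas equal whatever each arm happens to improve, and the control shift works in the intervention's favour.

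For the last row of step 3, shifting only the intervention arm by 3 cm removes 0.04 × 3 = 0.12 cm and leaves about 2.25 cm. A control shift of about −0.373/0.204 = −1.8 cm recovers 2.0 cm. Delta must therefore vary in both arms.

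**The case against.** A reader might infer that informative dropout is not examined at all. The documents do not support that. Zero change departs from MAR and, on the inputs above, puts missing intervention participants 3 cm behind completers. At 30% and 10% missing, LOCF gives 1.2 cm, against 2.0 − 0.9 = 1.1 cm for an intervention-only shift of 3 cm. In the simulated intervention-arm case, LOCF (2.018) is nearer the truth (1.995) than the other two analyses. What remains is that LOCF is one point, fixed by the data and not by the concern.

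A reader might also fault the plan because these analyses cannot test MAR. No analysis of observed data can, so that is no fault of this plan. Nor is every dropout set to zero: the Discontinuation criteria encourage those who stop the intervention to attend follow-up, and only people without a week 13 value are affected.

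The imputation model is not stated. If it used platform adherence, complete-case would need a stronger assumption than the imputation, and the contrast would tell more. That stands, but it would show the effect of the auxiliary variable, not of dropouts faring worse than comparable completers. The mixed models the section mentions also rely on MAR when fitted by likelihood.

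Finally, the size is small at planned attrition. The understated SE does not by itself inflate significance in the 10% example: the ratio of estimate to SE is about 2.18 for LOCF (1.8/0.827) and 2.24 for complete-case (2.0/0.894). An unseen SAP might add analyses, but the protocol itself names this pair as its robustness check.

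**Conclusion.** The concern holds in a limited form. The protocol names a sensitivity set that does not suit its own two-visit design. LOCF becomes baseline carried forward, an arbitrary single departure from MAR that can shrink, preserve or inflate the difference. Complete-case adds little beyond the MAR imputation. Agreement among them is weak evidence of robustness.

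At 10% missing in both arms, and assumed improvements of 3 and 1 cm, LOCF differs from the truth by 0.2 cm, which is modest beside an SE of about 0.9 cm. The larger figures (a false 0.40 cm benefit, a shared error of about 0.4 cm) rest on assumed unequal dropout and assumed missingness models. They show what the set can fail to reveal and do not predict what will happen in this trial.

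**What to change.** Under Data analysis, replace LOCF with a delta-adjusted tipping-point analysis built on the planned multiple imputation, with imputation done by arm. Vary delta for missing week 13 VAS separately in each arm, for example in 0.5 cm steps from 0 to 3 cm, including opposite shifts (intervention worse, control better). Report the combinations of delta at which the conclusion changes. Keep complete-case as supportive only.

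The cost is a few lines of code and a slightly longer results table; no new data are needed. The article states that nobody had been recruited at submission, so the change can still be prespecified. If it is judged a substantial change of analytical strategy, the protocol's own amendment process (ethics committee review and registry update) applies.
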